## Abstract

**Introduction:**

Detecting cancer earlier improves treatment options and long-term survival. A multicancer early detection test that reliably picks up early-stage cancer would potentially save lives and reduce the cost of treating cancer. One promising candidate is the *Enlighten* test, which applies machine learning to plasma amino acid concentrations to detect cancer. In a cohort of 77 patients recently diagnosed with breast, colorectal, pancreatic or prostate cancer, 60 (78%) were detected by the test (sensitivity), with no false positives in 20 healthy controls. The MODERNISED study will further develop the Enlighten test to detect 10 different cancers by adding bladder, lung, melanoma, oesophageal, ovarian and renal cancer to the test.

**Methods and analysis:**

MODERNISED (ISRCTN17299125) is a multicentre prospective, non-interventional, case–control study. We aim to recruit 1000 adult participants with a recent cancer diagnosis, 250 adult participants with symptoms of cancer where a cancer diagnosis was ruled out by the National Health Service (NHS) standard of care and 100 healthy adult volunteers. Cancer tissue of origin (ToO) will include bladder, breast, colorectal, lung, melanoma, oesophageal, ovarian, pancreatic, prostate and renal. Participants in the two non-cancer cohorts who are later diagnosed with cancer will be moved to the cancer cases cohort. The primary aim is to train and validate a machine learning algorithm to detect cancer, which will be evaluated by AUROC. Secondary aims include training and validating an algorithm to predict ToO and stage of cancer, exploring differences in performance by demographics and estimating how sensitivity varies across specificity cut-offs of 95%, 99% and 99.9%. These results will provide a statistically powered estimate of how well the Enlighten test can discriminate between individuals with and without cancer, which can then be validated for clinical use in further research.

**Ethics and dissemination:**

This study is sponsored by University Hospital Southampton NHS Foundation Trust and has been approved by the Health Research Authority and Health and Care Research West Midlands (24/WM/0234). Results will be presented at scientific meetings and published in international peer-reviewed journals. Lay summaries of study progress and findings will be published on the Southampton Clinical Trial Unit’s website.

**Trial registration number:**

ISRCTN17299125.

STRENGTHS AND LIMITATIONS OF THIS STUDYMulticancer early detection (MCED) tests are proposed as tools for improving the detection of cancer in the early stages, but most use cell-free DNA technology, which is expensive and has demonstrated poor sensitivity for stage I and stage II cancers.Amino acids may be more successful in detecting early-stage cancer because immune responses are stronger during the early stages of cancer.This study will use the Enlighten test, a new candidate MCED that applies machine learning to amino acid level patterns and has a sensitivity of 76% and specificity of 100% in a cohort of 72 cancer patients and 20 healthy controls.This study will retrain and evaluate the Enlighten test in newly diagnosed cancer patients, symptomatic patients who had cancer ruled out and healthy volunteers across southern England.Reliable and cheap MCED tests would potentially save lives and reduce the cost of treating cancer, but further validation in future research will be required before clinical implementation.

## Introduction

 Cancer is one of the leading causes of death worldwide, with 149 022 deaths attributed to cancer in England and Wales across 2023.^1^ Detecting cancer earlier improves the number of treatment options available and long-term survival.^2^ In 2019, the National Health Service (NHS) in the UK committed to increasing the proportion of cancers that are diagnosed at stage I or II.^3^ There has been minimal change in the proportion between 2019 (53.4%) and 2022 (54.8%), despite an increasing number of people referred for cancer diagnostics.^4 5^ Additional tools are required to detect cancer at an early stage, which would improve the proportion of cancers diagnosed at an earlier stage, improve patient outcomes and reduce the cost burden on the system.

### Multicancer early detection (MCED) tests

MCEDs, tests that analyse a ‘liquid-biopsy’ such as blood, urine, saliva or stool and test for the presence of multiple cancers in a singular sample, are being proposed as a complement to traditional cancer diagnosis pathways to improve early detection.^6^ A 2024 systematic review found 36 studies evaluating six different MCEDs, with most having a high risk of bias.^7^ There are no randomised studies demonstrating that using MCEDs leads to an increase in the proportion of cancers diagnosed at stage I or II. The majority of MCEDs that have published data available are using cell-free DNA (cfDNA) or circulating-tumour DNA (ctDNA), which are fragments of DNA released into the bloodstream that may possess alterations indicative of cancer.^8^

The degree of mutations present within cfDNA and ctDNA increases as cancer progresses, so this approach may not be successful if the aim is to detect cancers at stage I or II, where the amount of material shed into the bloodstream is below the limit of detection.^9^ The largest evaluation of an MCED in the UK, the SYMPLIFY study, used the GRAIL test on 5461 symptomatic patients referred for urgent investigation for a possible gynaecological, lung or gastrointestinal cancer. The sensitivity for cancer detection was much lower at stage I (24.2%) than at stage IV (95.3%).^10^ This is a common trend among cfDNA MCEDs. One meta-analysis found a pooled sensitivity of 50.3% for stage I or II versus 77.4% for stage III or IV.^11^ To increase early cancer detection, alternative techniques are required.

### The Proteotype Diagnostics Enlighten test

Proteotype Diagnostics (PD) have developed an alternative approach to MCED testing. Instead of measuring material released from tumours (cfDNA or ctDNA), amino acid concentrations are measured in plasma in the Enlighten test, which are affected by the immune response. Immune responses are stronger during the early stages of cancer^12^ and therefore may be used to improve the detection of stage I and II cancers. Machine learning (an ensemble subspace discriminant classifier) was applied to classify tested samples to cancer or non-cancer in a retrospective observational study of 77 cancer patients (breast, colorectal, pancreatic and prostate) and 20 healthy volunteers. A sensitivity of 78% at 100% specificity was achieved using Enlighten, and concentrations were further differentiated in early-stage cases.^13^

Southampton Experimental Cancer Medicine Centre (ECMC) responded to an open call for partnerships with PD to develop a study further evaluating the Enlighten test. Southampton Clinical Trials Unit (SCTU) then developed a research proposal with PD and ECMC as partners, which is academically sponsored by University Hospital Southampton Trust and jointly funded by the National Institute for Health and Care Research and the Office for Life Sciences (ref NIHR207538).

The primary aim of this study is to train a machine learning classifier to use amino acid concentrations from the Enlighten test to detect cancer (bladder, breast, colorectal, lung, melanoma, oesophageal, ovarian, pancreatic, prostate and renal) in comparison to adult participants with symptoms of cancer where a cancer diagnosis was ruled out and healthy volunteers. Participants will be randomised, with 75% used to train the classifier and 25% used to validate the classifier. Secondary aims include:

Training and validating a classifier to distinguish cancer patients from adult participants with symptoms of cancer, where a cancer diagnosis was ruled out.Training and validating a classifier to distinguish cancer patients from healthy controls.Evaluating discrimination and sensitivity by tissue of origin (ToO), stage, age, sex at birth and availability of a UK cancer screening programme.Training and validating a classifier to predict ToO.Training and validating a classifier to predict cancer stage.

## Methods and analysis

### Study design

MODERNISED (ISRCTN17299125) is a multicentre prospective, non-interventional, case–control study recruiting 1000 participants with known cancer, 250 under investigation for cancer where cancer was ruled out, and 100 healthy volunteers. Participants will be recruited from five secondary care sites and healthy volunteer register banks, or hospital or university staff in England. Recruitment began in January 2025. Recruitment is underway, and version 2 (01 April 2025) is the latest version of the study protocol at the time of submitting this manuscript. Important protocol modifications are reported to relevant parties as part of the SCTU’s standard operating procedures.

### Study participants

The first cohort, ‘cancer cases’, will consist of 1000 adults recently diagnosed with one of the 10 cancers, recruited from secondary care sites prior to treatment. The second cohort, ‘symptomatic controls’, will consist of 250 adults either currently or previously under investigation for one of the 10 cancers, recruited from secondary care sites, who are found to be cancer-free following normal diagnostic pathways. Participants in this cohort who are found to have cancer during follow-up will be moved to the cancer cases cohort. These participants will be reached via screening of clinic lists and approached during routine hospital visits for symptom investigation, or by phone call to invite them to attend an enrolment visit. The third cohort, ‘healthy volunteers’, will consist of 100 adults with no known cancer and no active symptoms indicative of cancer, recruited from volunteer groups at secondary care sites, or University and hospital staff if recruitment is slower than anticipated. These participants will be reached by advertisement of the study in email newsletters and invited to attend recruitment clinics. Participants in this cohort who are found to have cancer during follow-up will be moved to the cancer cases cohort. Full inclusion and exclusion criteria can be found in table 1. The study workflow is outlined in figure 1.

**Table 1 T1:** Inclusion and exclusion criteria

Entry arm	Inclusion criteria	Exclusion criteria
All	1. Age 18 years or older. 2. Able to provide a written informed consent. 3. Willing to provide a 4 mL blood sample at the time of enrolment.	6. Pregnancy (by self-report of pregnancy status), or pregnancy within the last 12 months. 7. Current febrile illness. 8. Infection requiring hospitalisation within 30 days prior to blood draw. 9. Acute exacerbation or flare of an inflammatory condition requiring escalation in medical therapy within 14 days prior to blood draw. 10. Undergone a surgical procedure (including diagnostic biopsy) within 14 days prior to blood draw. 11. Undergone a blood transfusion within 30 days prior to blood draw. 12. Recipient of organ transplant or prior allogeneic stem cell transplant. 13. Poor health status or unfit to tolerate a blood draw. 14. Oral or intravenous corticosteroid use in the past 14 days prior to blood draw.
Cancer cases	4. Have either of the following: **Confirmed cancer diagnosis of** breast, melanoma, colorectal, lung, prostate, pancreatic, ovarian, oesophageal, renal or bladder cancer (any stage I–IV) **within 90 days prior to or up to 90 days after study blood draw**, based on assessment of a pathological specimen (including, but not limited to, biopsy from primary tumour site, lymph node or metastatic lesion, or cytology specimen). Or **a high suspicion for a cancer diagnosis of** breast, melanoma, colorectal, lung, prostate, pancreatic, ovarian, oesophageal, renal or bladder cancer by clinical and/or radiological assessment, with *planned* biopsy or surgical resection to establish a definitive diagnosis within 3 months (90 days) *after* study blood draw.	15. Currently receiving, or ever received, any of the following therapies to treat their current cancer: surgical management of the cancer beyond that required to establish the cancer diagnosis; local, regional or systemic chemotherapy, including chemoembolisation; targeted therapy, immunotherapy, including cancer vaccines; hormone therapy or radiation therapy. 16. Known prior diagnosis of cancer, per guidance in protocol, separate from the confirmed or suspected cancer diagnosis associated with study enrolment. **Exception**: subjects with a history of non-melanoma skin cancer that has been effectively and exclusively managed by local or focal therapies, such as surgical resection, radiation therapy, cryotherapy or topical therapy, are eligible to enrol. 17. Cancer recurrence. 18. Synchronous malignancies.
Symptomatic control	**5**. Have either of the following: **Symptomatic of** breast, melanoma, colorectal, lung, prostate, pancreatic, ovarian, oesophageal, renal or bladder cancer, **but determined to be cancer-free** by clinical and/or radiological assessment and/or assessment of a pathological specimen (including, but not limited to, biopsy from suspected primary tumour site, lymph node or suspected metastatic lesion, or cytology specimen)—for a list of symptoms please refer to online supplemental file 1. Or **an initial high suspicion for a cancer diagnosis of** breast, melanoma, colorectal, lung, prostate, pancreatic, ovarian, oesophageal, renal or bladder that was **ruled out** 90 days after study blood draw.	19. Known current or prior diagnosis of cancer, per guidance in protocol. **Exception**: subjects with a history of non-melanoma skin cancer (eg, Basal Cell Carcinoma or Squamous Cell Carcinoma) that has been effectively and exclusively managed by local or focal therapies, such as surgical resection, radiation therapy, cryotherapy or topical therapy, are eligible to enrol.
Asymptomatic control		20. Known current or prior diagnosis of cancer, per guidance in protocol. **Exception**: subjects with a history of non-melanoma skin cancer that has been effectively and exclusively managed by local or focal therapies, such as surgical resection, radiation therapy, cryotherapy or topical therapy, are eligible to enrol.

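### One of the two routes into the symptomatic-control group sets no limit between investigation and blood draw, so recovered controls could inflate discrimination against symptomatic patients by an unknown amount

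*Protocol article*

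**What the plan says.** All references are to the protocol article, Methods and analysis.

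- **Study participants, text.** The symptomatic-control cohort "will consist of 250 adults either currently or previously under investigation for one of the 10 cancers, recruited from secondary care sites". These people are approached at hospital visits "or by phone call to invite them to attend an enrolment visit".
- **Table 1, criterion 3 (all cohorts).** "Willing to provide a 4 mL blood sample at the time of enrolment". A late enrolment therefore means a late sample.
- **Table 1, criterion 4 (cases).** A confirmed diagnosis must fall "within 90 days prior to or up to 90 days after study blood draw". The high-suspicion route needs a definitive diagnosis planned within the 90 days after the draw.
- **Table 1, criterion 5 (symptomatic controls).** The first limb takes people symptomatic of one of the ten cancers "but determined to be cancer-free" "by clinical and/or radiological assessment and/or assessment of a pathological specimen", with no interval to the draw. The second limb takes people with an initial high suspicion that was ruled out "90 days after study blood draw".
- **Status of the table.** "Full inclusion and exclusion criteria can be found in table 1".

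The Study design section describes the same 250 people simply as under investigation, without mentioning past investigation. Healthy volunteers must have no active symptoms. No matching statement says that symptomatic controls must have symptoms when they are bled.

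**The concern.** Three of the four routes into the case and symptomatic-control cohorts link the draw to the diagnostic episode. The first control limb does not. Admitting people with a past investigation and inviting them by phone allows the draw to come well after the episode.

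Timing matters because of the article's own rationale. The Introduction says that the plasma amino acids respond to the immune response. The common exclusions for febrile illness, recent inflammatory flare and recent corticosteroids treat inflammatory state at the draw as relevant. On that reasoning, a control whose symptoms have settled may look more like a healthy volunteer than like a patient under investigation.

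Cancer against symptomatic controls is a named secondary aim, and it is the contrast closest to the triage use proposed in the Discussion. Symptomatic controls are also most of the non-cancer group, so the primary AUROC is exposed. The 3:1 random split gives no protection, because training and validation sets draw on the same mix of controls. The Analysis plan stratifies by control type, but the strata it lists do not include time since investigation.

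**Working it through.** **1. The plan's own figures.** These reproduce, and the point does not depend on them.

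- Training size: n = p / [(S − 1) ln(1 − R²/S)], with p = 15, S = 0.90 and R² = 0.20 × 0.682 = 0.136 at prevalence 0.74. This gives 916, and 916 × 0.74 = 678 events, as stated.
- Validation precision: the closed-form (Newcombe) standard error with 337 people, 250 of them cases, gives a 95% CI width of 0.098 at AUROC 0.84 and 0.1005 at 0.83. This agrees with the stated minimum of 0.84 for a width of 0.1.

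**2. Timing rules side by side.**

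| Route | Tie to the blood draw |
|---|---|
| Case, confirmed | 90 days either side |
| Case, high suspicion | definitive diagnosis planned within 90 days after |
| Control, second limb | ruled out 90 days after |
| Control, first limb | none stated |

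Exclusion 10 bars a draw within 14 days after a biopsy. A first-limb control who had a biopsy therefore has a minimum wait but no maximum.

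**3. Inputs for an illustration.**

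- From Sample size calculation: 62 symptomatic controls and 25 healthy volunteers in validation, so 62/87 = 71% of validation controls are symptomatic controls.
- Assumed, because the article gives none of them: a = 0.80, AUROC of cases against controls bled while symptomatic; b = 0.90 to 0.98, AUROC against recovered controls; f = 25% to 50%, share recovered. The upper b is the pilot AUROC, and the pilot's controls were 20 healthy volunteers.

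**4. Symptomatic-control AUROC.** For a fixed score, observed AUROC = (1 − f)a + fb, so the inflation is f(b − a).

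| f | b = 0.90 | b = 0.98 |
|---|---|---|
| 25% | 0.75 × 0.80 + 0.25 × 0.90 = 0.825 (+0.025) | 0.75 × 0.80 + 0.25 × 0.98 = 0.845 (+0.045) |
| 50% | 0.50 × 0.80 + 0.50 × 0.90 = 0.85 (+0.05) | 0.50 × 0.80 + 0.50 × 0.98 = 0.89 (+0.09) |

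**5. Pooled primary AUROC.** With 0.98 for both recovered controls and healthy volunteers:

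- f = 0: (62 × 0.80 + 25 × 0.98)/87 = 0.852
- f = 25%: (62 × 0.845 + 25 × 0.98)/87 = 0.884 (+0.032)
- f = 50%: (62 × 0.89 + 25 × 0.98)/87 = 0.916 (+0.064)

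The shift equals (62/87) × f(b − a). With b = 0.90 it is therefore 0.018 to 0.036.

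**6. Benchmarks.** The plan's target half-width of 0.05 belongs to the pooled AUROC, so only the shifts in step 5 should be set against it. For the symptomatic contrast, use Hanley-McNeil: SE² = [A(1 − A) + (n₁ − 1)(Q₁ − A²) + (n₀ − 1)(Q₂ − A²)]/(n₁n₀), with Q₁ = A/(2 − A) and Q₂ = 2A²/(1 + A). At A = 0.80, n₁ = 250 and n₀ = 62, SE² = (0.16 + 6.64 + 4.338)/15,500. The CI width is 0.105, a half-width of about 0.053.

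**7. No-effect case.** The inflation is zero if f = 0 or if a = b.

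**The case against.** The strongest reply is that the wording may already exclude recovered people. Criterion 5 begins with being symptomatic, and the Introduction and Study design describe these controls as having symptoms or being under investigation. Recruitment uses clinic lists and 28-day faster diagnosis lists, so many draws will fall close to work-up. A phone invitation need not mean late recall, since the 14-day biopsy exclusion forces some people to return. The full protocol (version 2) is not shown and may say more.

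This limits the likely size but does not close the gap. Nothing shown requires symptoms at the draw, and past investigation is expressly admitted. Table 1 is presented as the full criteria. Where it relies on another source, for prior cancer or the symptom list, it says so, and criterion 5 has no such pointer for timing.

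Three stronger readings are tempting but are not supported:

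- *Every symptomatic control may be bled at any time.* The second limb is tied to the draw, and the article does not give the split between limbs.
- *Specificity will be overstated.* The Analysis plan fixes specificity at 95%, 99% and 99.9%. Any effect would appear in AUROC and in sensitivity at those cut-offs.
- *The inflation is known to match or exceed the planned precision.* The inputs in step 3 are assumptions, and using 0.98 for recovered controls presumes that they resemble healthy volunteers.

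**Conclusion.** The point holds as a gap in eligibility that permits a bias. It does not show that bias has occurred. As written, the first limb of criterion 5 allows a draw at an unlimited interval after investigation, unlike the other three routes. If amino acid levels move towards normal once symptoms settle, AUROC and sensitivity at the fixed cut-offs would be too favourable. The effect would be largest against symptomatic controls and smaller in the pooled analysis.

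Under the assumptions in step 3, the symptomatic-control AUROC is inflated by 0.025 to 0.09. The pooled AUROC is inflated by about 0.03 to 0.06 if recovered controls and healthy volunteers both separate from cases at 0.98. The true figure could be zero, and the article gives no means of narrowing the range. It is worth acting on because the remedy is cheap and affects what can be concluded about use in symptomatic patients.

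**What to change.** **For all symptomatic controls, including those already enrolled.** Unless already captured, record (a) the interval from cancer-free determination, or end of investigation, to blood draw and (b) whether symptoms were present at the draw. Repeat the primary and symptomatic-control AUROC, and sensitivity at the three cut-offs, restricted first to draws within 90 days and then to controls symptomatic at the draw.

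**For remaining recruitment.** Reconcile the Study participants text, which admits past investigation, with the Study design description and criterion 5. The simplest way is to apply the study's own 90-day window to the first limb. The window alone is not enough: symptoms can settle within 90 days, so symptom status still has to be recorded.

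**Cost.** Two data items and one sensitivity analysis with fewer controls and wider intervals. For example, if half of the 62 validation controls dropped out, the step 6 formula with n₀ = 31 gives SE² = (0.16 + 6.64 + 2.133)/7,750 and a CI width of 0.133 instead of 0.105. Adding the window also needs a protocol amendment during recruitment, leaves early and late participants under different criteria, and may slow control recruitment slightly. No sample size changes.

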### Model training and validation

Participants will be randomised in a 3:1 ratio with varying permuted blocks, balanced by cancer ToO and stage, into a model training (75% of participants) or model validation (25% of participants) set. The randomisation list will be pregenerated by a statistician at SCTU. Those in the model training set will have their cohort (cancer case, symptomatic control and asymptomatic control), age and sex shared with PD to train machine learning algorithms in combination with amino acid concentrations. PD will be blinded to the diagnostic status of participants in the model validation set.

Symptomatic controls and healthy volunteers may later be diagnosed with cancer (and therefore move into the cancer cases cohort). Randomisation will therefore only occur on three occasions during the study to reduce the impact of imbalance between building and validation sets. All participants and care providers will remain blinded. Participants will not be randomised more than once. The occasions are as follows: (1) when the amino acid concentrations have been measured for the first batch of 20 participants’ samples with complete data (to stress test processes). (2) When the T_1_ visit has occurred for 50% of the target participants in the breast, colorectal, prostate and lung cancer cohorts. (3) When the T_1_ visit has occurred for all participants, and all data have been returned.

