### Machine learning training and validation

Machine learning techniques considered will include: random forests, support vector machines, ensemble subspace discriminant classifiers, XGBoost, neural networks and deep learning algorithms. The final modelling strategy will be informed by comparative predictive performance and computational cost. Triplicate values of the five amino acids (Cysteine, Reduced Cysteine, Lysine, Tryptophan and Tyrosine) will be used as input parameters (or combined as average readings), with potential additions of participant age and sex. Feature importance will be measured by Shapley values. Stratified cross-validation will be used to reduce overfitting.

One algorithm will predict diagnostic status (‘cancer’ or ‘no cancer’), a second will predict cancer ToO (bladder, breast, colorectal, lung, melanoma, oesophageal, ovarian, pancreatic, prostate and renal) and a third will predict cancer stage (I, II, III, IV). The trained algorithms will use amino acid concentrations (and potentially age and sex) to predict diagnostic status, ToO and cancer stage in the development and validation cohorts. These predictions will be provided to statisticians at SCTU to independently validate predictions against true status.

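### Table 1 lets a cancer case be bled after a diagnostic procedure that may already have removed the tumour, and the sample still counts as cancer in training and validation

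*Protocol article*

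**What the plan says.** All the relevant rules are in the protocol article, section Study participants, including Table 1.

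- Inclusion 4, first branch: a confirmed diagnosis of one of the ten cancers "within 90 days prior to or up to 90 days after study blood draw". Confirmation rests on pathology, and the list of accepted specimens is open-ended.
- Inclusion 4, second branch: high clinical or radiological suspicion, with a planned "biopsy or surgical resection to establish a definitive diagnosis within 3 months (90 days" of the draw. Here the procedure comes after the sample.
- Exclusion 15: bars treatment of the current cancer. Its surgical limb reaches only "surgical management of the cancer beyond that required to establish the cancer diagnosis".
- Exclusion 10, all participants: "Undergone a surgical procedure (including diagnostic biopsy) within 14 days prior to blood draw".
- Running text: cases are "recruited from secondary care sites prior to treatment".

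The label follows from enrolment and diagnosis. Under Model training and validation, training participants "will have their cohort (cancer case, symptomatic control and asymptomatic control), age and sex shared with PD", the company that builds the classifier. Under Machine learning training and validation, the trials unit's statisticians "independently validate predictions against true status".

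**The concern.** The Introduction explains the test by a host immune response that alters plasma amino acids and is said to be stronger in early disease. A sample drawn after the tumour has been completely removed cannot show whether the test would have found that tumour. It may carry a fading tumour signal, no signal, or a trace of wound healing.

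If such samples enter the case group unmarked, the classifier partly learns from them and the validation set scores them as detected or missed cancers. Complete removal at diagnosis is most plausible for small, early tumours. The results most exposed are therefore those by stage and by tissue of origin, and early-stage detection is the study's stated rationale. Excision of a skin lesion, transurethral resection of a bladder tumour and removal of a malignant polyp are natural examples. They are mine and are not named in the article, though melanoma, bladder and colorectal cancer are all study cancers.

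**Working it through.** **1. Do the rules, read together, allow it?**

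- Inclusion 4, first branch, allows the diagnosis to come before the draw by up to 90 days.
- Exclusion 15 does not reach surgery needed for the diagnosis, however complete the removal.
- The second branch of inclusion 4 itself recognises resection as a way to make the diagnosis. It requires the draw first; the first branch sets no such order.
- Exclusion 10 sets only a lower bound. A case already biopsied is bled more than 14 days and up to about 90 days later. The 90 days run from the confirmed diagnosis, so the interval from the procedure can be slightly longer.
- No criterion requires tumour to be present at the draw.
- Outcome measurement lists diagnosis codes, morphology and staging. Neither it nor the Analysis plan mentions residual tumour, so as described the affected cases would not be separated.

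The rules allow it.

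**2. The plan's own figures.** Sample size calculation gives 15 parameters, prevalence 0.74, Nagelkerke R² 0.20, shrinkage 10% (S = 0.9), and a minimum of 916 (678 events).

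- Maximum Cox–Snell R² = 1 − exp{2[0.74 ln 0.74 + 0.26 ln 0.26]} = 0.682; 20% of it is 0.1364.
- n = 15 / [(0.9 − 1) ln(1 − 0.1364/0.9)] = 913. With R² rounded to 0.136, n = 916, and 916 × 0.74 = 678 events. Reproduced.
- For validation (337 people, prevalence 0.74), a Newcombe-type variance gives a 95% CI width of 0.0975 at AUROC 0.84 and 0.1003 at 0.83. This agrees with the stated threshold of 0.84 for a width of 0.1.

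**3. Illustration of size.** Let f be the share of all cases bled after complete removal (an assumption; no figure is given) and a the AUROC of those samples against controls. Then

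observed AUROC = (1 − f) × true AUROC + f × a.

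If affected samples score like controls, a = 0.5:

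| f | from true 0.84 | CI width | from pilot 0.98 |
|---|---|---|---|
| 5% | 0.798 + 0.025 = 0.823 | 0.102 | 0.956 |
| 10% | 0.756 + 0.050 = 0.806 | 0.106 | 0.932 |
| 20% | 0.672 + 0.100 = 0.772 | 0.114 | 0.884 |

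The widths are for the 0.84 column, by the Newcombe-type formula. The Hanley–McNeil formula (250 cases, 87 controls) gives 0.089, 0.094 and 0.103, so whether 0.1 is exceeded at 5% depends on the formula.

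At the other extreme, a healing signal that separated these samples perfectly from controls (a = 1) would give 0.848, 0.856 and 0.872 from a true 0.84. At f = 10% the observed value could thus lie anywhere from 0.806 to 0.856. The formula covers scoring only, not any harm to training.

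**4. Training events if affected cases are left out.** Of 750 planned training cases, 5% leaves about 712, 10% leaves 675 and 20% leaves 600. The minimum of 678 is lost once more than 72 (9.6%) are removed.

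**The case against.** The text can be read more strictly. A site might hold that complete removal, where a small sample would have sufficed, goes beyond what the diagnosis needed, and the statement about recruitment before treatment points the same way. The full protocol, version 2, is not shown. This stands in part: the wording is ambiguous rather than an open invitation. But the section presents Table 1 as the full criteria, and where removal is itself the diagnostic act the stricter reading has no hold.

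The 14-day gap deals with part of the acute effect of a procedure. It does nothing about absent tumour.

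A reader might infer that the affected samples are plain labelling errors and that sensitivity in melanoma and bladder cancer must be understated by a known amount. The documents do not support that:

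- A case is defined by recent diagnosis, and these patients meet the definition.
- Nothing says how often removal is complete or how fast the amino acid signal fades.
- Equal numbers per cancer are not stated.
- The pilot sensitivity of 78% was obtained at 100% specificity, in a pilot with AUROC 0.98 and no melanoma or bladder cases. It cannot be joined to an AUROC of 0.84, which under an equal-variance binormal model implies about 41% sensitivity at 95% specificity.

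Finally, the primary aim is the overall AUROC, results are broken down by tissue of origin, and further validation is promised before clinical use. That limits the harm. But a weak result in one cancer would not reveal whether the test failed or the tumour had gone.

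**Conclusion.** The gap in the criteria is real: inclusion 4, exclusion 15 and exclusion 10 together admit samples taken after the tumour may have been removed. This fits poorly with the statement on recruitment before treatment and with the order required in the second branch of inclusion 4. Such samples cannot show detection of a tumour in place.

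Its size is unknown. The loss of 0.017 to 0.068 in AUROC (0.84 to 0.823 or 0.772) rests on an assumed 5% to 20% of all cases and on those samples scoring like controls. The sign could reverse. A reader might conclude that the primary result is invalid, or that these cases must be struck from it; neither follows, and at about 10% affected, removal would take training below the plan's own minimum. This is a cheap improvement that mainly protects the early-stage and by-cancer results. Confidence is high in the wording gap and low in its effect.

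**What to change.** 1. Reconcile inclusion 4 and exclusion 15 with the statement that cases are recruited before treatment. State whether a case whose tumour may have been completely removed at diagnosis is eligible, and take the research sample before the procedure where feasible. This concerns research sampling only and should not alter the timing of care.
2. At the three-month record retrieval (T1), record the type and date of the diagnostic procedure and whether residual tumour was known to be present at the draw.
3. Keep the primary analysis as planned. Prespecify a sensitivity analysis of validation AUROC and sensitivity (overall, by stage and by tissue of origin) without cases lacking known residual tumour, and report those cases as a separate group. Refit the classifier without them only if enough training events remain against the minimum of 678.

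The cost is a short clarification, one or two data fields, some missing residual-tumour data, and fewer cases in the sensitivity analysis. The study has been recruiting since January 2025 and a pre-procedure sample cannot be obtained afterwards, so the first step is worth taking soon. The other two can also cover participants already enrolled, as far as their records allow.
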